### Trial design

7.2

This study adopts a randomized controlled trial design and is conducted at the Inner Mongolia Maternal and Child Health Care Hospital, Inner Mongolia Autonomous Region, China. The intervention involves implementing a Pay-It-Forward deposit system for women undergoing HPV self-sampling. A total of 108 participants are enrolled and randomly assigned into two groups: the intervention group with 54 participants receiving HPV self-sampling kits through prepayment of a deposit, and the control group with 54 participants receiving HPV self-sampling kits for free. **Figure 1** presents the detailed flowchart of this study. The details of the research process are shown in **Figure 1**.

**Figure 1 f1:**
[figure not shown]
Flowchart.

### Recruitment

7.3

Participants will be recruited at the Maternal and Child Health Family Planning Service Centers in four urban districts (Xincheng District, Saihan District, Huimin District, and Yuquan District) and five counties (Wuchuan County, Qing Shui He County, Helin County, Tuoketuo County, and Tuo Zuo Banner) of Hohhot City, Inner Mongolia Autonomous Region, China, starting from January 20, 2025.A multi-channel recruitment approach will be employed, including online WeChat public accounts, hospital outpatient clinics, and community health service centers. After identifying eligible and interested individuals, physicians at each Maternal and Child Health Care and Family Planning Service Center further explained the study objectives and procedures. Subsequently, eligible women were screened and selected based on predefined criteria. Each participant received a detailed informed consent form ((refer to Appendix), which outlined the study’s objectives, procedures, and potential implications. Women who reached mutual agreement and signed the informed consent form constituted the recruited cohort. Participants will be then randomly assigned to either the intervention group (“Pay-It-Forward” group) or the control group (“free”group).

### Eligibility criteria

7.4

The inclusion criteria for this perinatal maternity study include: (1) Women aged 24 years or older; (2) Hold Chinese nationality and have resided in Hohhot for at least six months; (3) Have not undergone HPV self-sampling or cervical cancer screening in the past 12 months; (4) Have not received the HPV vaccine; (5) Possess a mobile phone number and are able to use a smartphone; (6) Are capable of understanding and signing the informed consent form; (7) Without any severe physical or mental illnesses and are able to complete the entire study process. Exclusion criteria are: (1) Women with a history of cervical cancer or cervical intraepithelial neoplasia (CIN); (2) Pregnant women; (3) In other clinical studies related to HPV.

### Sample size

7.5

The primary outcome is the feedback rate of HPV self-sampling. According to the results of previous studies (9), we hypothesize that the “Pay-It-Forward” intervention will increase the feedback rate to 90%, the feedback rate of HPV self-sampling results in the control group is 61.7%. Using the PASS 15.0 software and applying a two-sided test with α = 0.05 and a power of the test (1 - β) = 0.80, the required sample size per group was calculated to be 86 participants. Considering a potential dropout rate of 20%, we ultimately determined that 54 participants should be recruited per group, resulting in a total sample size of 108 participants.

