#### Primary outcome

7.11.1

The primary outcome of this study is the feedback rate of HPV-based self-sampling. It refers to the percentage of participants who mail back the tested HPV sampling kits to us within 1 month after receiving the HPV self-sampling kits, relative to the total number of HPV self-sampling kits distributed. If the feedback is not received within 1 month after distribution, it is considered as no feedback by default.

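### The stated requirement of 86 women per group cannot become 54 per group after a 20% dropout allowance and does not follow from the stated inputs; 86 is probably the two-group total

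*Protocol article*

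**What the plan says.** Section 7.5 of the protocol article sets out the whole calculation in one paragraph.

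- Endpoint: "The primary outcome is the feedback rate of HPV self-sampling".
- Rates: the "intervention will increase the feedback rate to 90"%, and "the feedback rate of HPV self-sampling results in the control group is 61.7"%.
- Error rates: "applying a two-sided test with α = 0.05 and a power of the test (1 - β) = 0.80", computed in PASS 15.0. The test and any continuity correction are not named.
- Result: "the required sample size per group was calculated to be 86 participants".
- After a 20% dropout allowance: "we ultimately determined that 54 participants should be recruited per group, resulting in a total sample size of 108 participants".

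The Trial design section (7.2) repeats the enrolment figure, with "the intervention group with 54 participants receiving HPV self-sampling kits through prepayment of a deposit" and 54 controls. The Abstract also gives 108 in total. For the endpoint itself, section 7.11.1 takes kits distributed as the denominator and adds: "If the feedback is not received within 1 month after distribution, it is considered as no feedback by default".

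**The concern.** The paragraph starts from a requirement of 86 per group, adds a margin for losses, and ends at 54 per group. The second number should be larger than the first. Read literally, each arm would be (86 − 54)/86 = 37% short of its own stated requirement before anyone drops out. If 86 per group really were needed, a 20% allowance would call for 86/0.8 = 107.5, that is 108 per group and 216 in total, twice what is planned.

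This paragraph is the only justification for the size of the trial, and the Discussion names the small sample as a possible limit on power. Readers will check it, and as printed they cannot tell whether a label, a number or the enrolment target is at fault.

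**Working it through.** **Inputs.** From section 7.5: p1 = 0.617, p2 = 0.90, two-sided alpha 0.05 (z = 1.960), power 0.80 (z = 0.8416), dropout 20%. From section 7.6: 1:1 allocation. Derived: difference 0.283, squared 0.08009; mean rate 0.7585.

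**Step 1: try to reproduce 86 per group.**

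- Pooled z test (uncorrected chi-square): n = [1.960·√(2·0.7585·0.2415) + 0.8416·√(0.617·0.383 + 0.90·0.10)]² / 0.283² = (1.960·0.6053 + 0.8416·0.5712)² / 0.08009 = 1.667² / 0.08009 = 34.7, so **35** per group.
- With continuity correction: n′ = (n/4)·[1 + √(1 + 4/(n·0.283))]² with n = 34.7, giving 41.5, so **42** per group.
- Unpooled variance: (1.960 + 0.8416)²·0.3263 / 0.08009 = 32.0, so 32 per group.
- Arcsine: 33 per group.
- Fisher's exact test, by enumeration: power is 81% at 40 per group.
- One-sided versions of the formulas: 26 to 34 per group.

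None comes near 86 per group at 80% power. At 86 per group, power is about 99% (exact: 99.5% uncorrected chi-square, 99.2% continuity-corrected, 99.2% Fisher).

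**Step 2: the dropout step.**

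| Reading of 86 | Before dropout | Divided by 0.8 | Stated enrolment |
|---|---|---|---|
| Per group | 86 per group | 107.5 → 108 per group, 216 in total | 54 per group, 108 in total: no match |
| Total | 43 per group | 53.75 → 54 per group, 108 in total | 54 per group, 108 in total: match |

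Multiplying by 1.2 instead gives 86 × 1.2 = 103.2, rounded up to 104, which does not match.

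**Step 3: which reading do the inputs favour?** The match in step 2 is not proof on its own. A requirement of 86 per group also inflates to 108, and that 108 could then have been mistaken for a total. The inputs separate the two readings: the continuity-corrected total is 2 × 42 = 84, two short of 86, whereas no method gives a per-group figure near 86. The total is therefore much the likelier reading, although 43 per group is not reproduced exactly.

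**Step 4: power for the size enrolled, at 61.7% against 90% (exact enumeration).**

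| Analysed per group | Uncorrected chi-square | Continuity-corrected | Fisher |
|---|---|---|---|
| 43 | 89.7% | 82.9% | 83.9% |
| 54 | 94.9% | 91.8% | 91.8% |

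Normal approximations (uncorrected and continuity-corrected) give 82–88% at 43 per group and 91–94% at 54.

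**The case against.** The best defence is that this is a slip of two words. The enrolment figure is the same in the Abstract, Trial design and Sample size sections, it follows from 86 by a correct dropout formula once 86 is read as the total, and it gives more than 80% power at the stated rates. All of that stands, and it makes this a fault in reporting rather than in the trial's ability to answer its question. It does not rescue the sentence: the printed requirement is more than twice what the inputs give, and the document nowhere says that 86 is a total.

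The defence also limits what may be claimed. A reader might infer that the trial is underpowered, or that its size and its 80% power cannot both be true. That applies only to the literal 86 per group. The 54 per group that will be enrolled meets 80% power on the stated rates.

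A reader might also infer that the dropout allowance conflicts with the endpoint rule, because non-return counts as no feedback and so lost women never leave the analysis. The denominator in section 7.11.1 is kits distributed. A woman randomised who never receives a kit, for instance because she does not prepay as section 7.7 requires, falls outside it, and an allowance for such losses is compatible with the rule. For losses after the kit is handed over, the allowance is merely conservative at the stated rates.

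Finally, a reader might cut both assumed rates by a further 20% for dropout and conclude that power falls well short of 80%. The text does not support this. Section 7.5 calls both figures feedback rates, and section 7.11.1 defines that rate with non-return already counted as failure, so the further cut would count the same women twice.

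**Conclusion.** Wrong as written. The figure of 86 per group contradicts both the 54 per group that follows it and the inputs that precede it (35 to 42 per group by the uncorrected and continuity-corrected formulas, about 99% power at 86). The likely cause is a total labelled as a per-group number. That rests on the dropout arithmetic and on the near match with a continuity-corrected total of 84, not on any statement in the document.

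On that reading 108 women are enough: about 83–90% power with 43 per group analysed and 92–95% with all 54. This assumes that the printed rates of 61.7% and 90% are the ones entered in the software. If 86 per group was truly intended at those rates, it is the 80% power statement that does not match and must be corrected, since the power would be about 99%.

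**What to change.** Rerun the PASS calculation and name the test, including whether a continuity correction was used. Then correct the sentence. If the rerun confirms it, suitable wording would be: 86 participants in total, 43 per group; with 20% dropout, 43/0.8 = 53.75, hence 54 per group and 108 in total. If the rerun gives another number, print that number instead.

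Restate the power for the size enrolled. Because a woman who receives a kit and does not return it counts as no feedback, give the power with all 54 per group analysed (92–95%, depending on the test) beside the figure for 43 per group.

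The cost is one software run and one rewritten paragraph, with no change in enrolment if 86 is confirmed as the total. If 86 per group was meant, the sponsor must correct the power statement and reconcile that requirement with the 54 per group planned.

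### Section 7.5 states a requirement of 86 per group but recruits 54 per group after a dropout allowance; 86 fits only as the total for both groups

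*Protocol article*

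**What the plan says.** Section 7.5 (Sample size) gives a complete chain from inputs to recruitment target.

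- Endpoint: "The primary outcome is the feedback rate of HPV self-sampling", a proportion in each group.
- Rates, in per cent: the "intervention will increase the feedback rate to 90", while "the feedback rate of HPV self-sampling results in the control group is 61.7".
- Test settings: PASS 15.0, "applying a two-sided test with α = 0.05 and a power of the test (1 - β) = 0.80".
- Result: "the required sample size per group was calculated to be 86 participants".
- Allowance and target: "Considering a potential dropout rate of 20" per cent, "we ultimately determined that 54 participants should be recruited per group, resulting in a total sample size of 108 participants".

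Section 7.2 (Trial design) repeats the target: "A total of 108 participants are enrolled and randomly assigned into two groups", with 54 in each. The abstract also gives 108. Section 7.6 fixes 1:1 allocation.

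**The concern.** The chain goes down where it can only go up. Allowing for dropout means recruiting more people than must be evaluated, yet 86 per group turns into 54 per group. At least one of the two figures, or the label on one of them, must be wrong.

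Section 7.5 is the article's only justification of the trial's size. Taken at its word, the trial would recruit 54/86 = 63% of its own requirement before dropout and 54/108 = 50% of the requirement after dropout. An ethics committee, funder or later reader could not tell from the sentence whether the trial is properly sized. They also could not reproduce the stated requirement from the stated inputs.

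**Working it through.** **Inputs (all from section 7.5, with 1:1 allocation from section 7.6).** p1 = 0.617, p2 = 0.90, difference d = 0.283, mean p = 0.7585. Two-sided 5% gives z = 1.960; 80% power gives z = 0.8416.

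**Step 1. The plan's own dropout step.** Recruited number = evaluable number / (1 − 0.20).

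| Reading of 86 | Before dropout, per group | After dropout, per group | Total | Agrees with 54 and 108? |
|---|---|---|---|---|
| Per group, as printed | 86 | 86/0.8 = 107.5, so 108 | 216 | No |
| Both groups together | 43 | 43/0.8 = 53.75, so 54 | 108 | Yes, exactly |

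Working backwards gives the same answer: 54 × 0.8 = 43.2 per group and 108 × 0.8 = 86.4 in all.

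**Step 2. The requirement from the printed inputs.**

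Variance terms: p1(1 − p1) = 0.2363 and p2(1 − p2) = 0.0900, sum 0.3263; 2 × 0.7585 × 0.2415 = 0.3664; d² = 0.0801.

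- Unpooled z: (1.960 + 0.8416)² × 0.3263 / 0.0801 = 31.98, so 32 per group.
- Pooled z: (1.960 × √0.3664 + 0.8416 × √0.3263)² / 0.0801 = 34.70, so 35 per group.
- Continuity-corrected: (34.70/4) × [1 + √(1 + 4/(34.70 × 0.283))]² = 41.47, so 42 per group.
- Fisher's exact test, power by full enumeration of the two binomials: 0.799 at 39 and 0.812 at 40, so 40 per group.

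None gives 86 per group. The nearest to 43 is the continuity-corrected 42, so 43 is plausible but is not reproduced exactly.

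**Step 3. Power at the sizes in question (exact binomial enumeration, 61.7% v 90%, two-sided 5%).**

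| Per group | Pearson | Fisher |
|---|---|---|
| 43 | 0.897 | 0.839 |
| 54 | 0.949 | 0.918 |
| 86 | 0.995 | 0.992 |

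At 86 per group the power would exceed 99%, not the stated 80%. This is a second sign that 86 is not a per-group requirement under these inputs.

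**The case against.** The strongest reply is that nothing operational is in doubt. The figures of 54 and 108 agree in section 7.5, and the design section and the abstract repeat them. They follow exactly from 86 as a total, and on the printed rates they give ample power. On that view this is a slip of two words. Most of this stands: no design, enrolment or analysis decision changes if 86 was the total. It does not rescue the sentence, which is false as printed and which no other section corrects.

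A second reply is that a condensed article may leave the choice of test to the full protocol. That is fair, and the unnamed test is not an error in itself. It matters here only because 43 does not come out of any method tried, so the option used has to be known before the corrected figure can be confirmed.

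A third is that one formula does give 86 per group: the continuity-corrected calculation at 99% power. Section 7.5 states 80%, so this does not reconcile the text either.

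A reader might go the other way and infer that the trial is badly underpowered, perhaps taking the Discussion's remark on a relatively small sample as confirmation. The documents do not support that. The inference needs 86 per group to be right and the printed rates or power to be wrong. Nothing in section 7.5 suggests this, and the dropout arithmetic points against it. The Discussion's remark is a general limitation and gives no figure.

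**Conclusion.** The point holds as an error in a stated figure. The requirement of 86 per group is inconsistent with 54 per group after a 20% allowance (it would lead to 108 per group, 216 in all). It also does not follow from the printed inputs, which give about 32 to 42 per group. The figure 86 fits only as the total, so a mislabelled total is the most likely cause. The article alone cannot prove this; only the software output can.

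No shortfall in power is shown. At 61.7% v 90%, power is about 84% to 90% with 43 evaluable per group and 92% to 95% with all 54, depending on the test. These values assume that the planning rates are correct and already count a kit not returned as no feedback, as section 7.11.1 defines the outcome. Because that definition keeps non-returners in the denominator, the number analysed for the primary outcome may be nearer 54 than 43.

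**What to change.** Retrieve the PASS output and correct section 7.5 to match it.

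- **If 86 was the total:** state 86 in total (43 per group), raised for 20% dropout to 54 per group (108 in total). Name the test and options that give the figure. The continuity-corrected formula gives 42 and Fisher's exact test gives 40, so 43 should be either reproduced or replaced. Add the power at 43 and at 54 per group under the named test.
- **If the output really was 86 per group:** the printed rates or power did not produce it. Correct those inputs and restate the power that 54 per group delivers under them. Whether 54 is enough would then have to be judged afresh.

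The cost is one rerun of the software and one or two corrected sentences. On the total reading, enrolment need not change; that assurance does not extend to the second case.

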### Randomization

7.6

After completing the baseline study visit, participants were randomly allocated to one of the two study groups using a 1:1 ratio. The randomization procedure utilized a random number table approach. The detailed steps are as follows:

Random Number Generation: A basic randomization technique was employed. The study designer created a sequence of random numbers using the RANDBETWEEN function in Excel.Sealed Envelopes: These random number sequences were placed in identical, sealed, opaque envelopes that were sequentially numbered. Both the participants and the interveners are unaware of the participants’ group assignments.Enrollment Process: Upon enrollment of each participant, the researcher sequentially opened the envelopes in accordance with a predefined procedure.Assignment: Based on the number revealed in the opened envelope, the participant was assigned to the corresponding study group, and the researcher documented the assignment outcome.

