### Interventions

7.7

Compared with the control group, the intervention frequency is only once. That is, when distributing the HPV self-sampling kit, the intervention group needs to prepay to obtain the kit, while the control group can receive the HPV self-sampling kit without payment. Considering that the market price of an HPV self-sampling kit is around 20 RMB, we set the prepayment fee at 20 RMB. This can well simulate the real situation when the participants purchase the kit by themselves in daily life. Moreover, a proper deposit can avoid the problems caused by a high deposit: ① exceeding the participants’ affordability and thus reducing their willingness to participate; ② increasing the participants’ psychological pressure and causing unnecessary worries, which may affect the accuracy of the study results. On the other hand, a proper deposit can also avoid the problems caused by a low deposit: lack of effective constraints, leading to participants not taking the trial seriously and thus causing unstandardized sampling operations and other problems that may affect the trial results. We use the deposit as an incentive to encourage participants to actively provide feedback on the results of HPV self-sampling and to increase the feedback rate of HPV self-sampling results. The intervention flow chart is shown in **Figure 2**. To enhance participants’ psychological commitment and ensure active participation, the full prepayment amount will be refunded upon completion and feedback of the self-sampling results. Participants can choose from various convenient payment methods, including cash, bank transfer, or third-party payment platforms, to minimize payment costs and barriers. After self-sampling, participants in the intervention group can return the sampling kit to the corresponding Maternal and Child Health Care and Family Planning Service Center, which will then forward it to the Genetic and Eugenics Office of the Inner Mongolia Maternal and Child Health Care Hospital. A dedicated hotline will be established to facilitate timely feedback from participants. For those with positive HPV results, free follow-up medical services, including physician consultations and examination appointments, will be provided to ensure they receive proper treatment. Additionally, ongoing monitoring of participants’ adherence to treatment will be conducted.

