### Data monitoring

7.16

A Data Monitoring Committee (DMC) will be established for this study, comprising at least two members from the Medical Ethics Committee of the Inner Mongolia Maternal and Child Health Hospital. Operating independently of the study team, the DMC will regularly assess trial progress and safety data according to the established Data Monitoring Plan (DMP). The scope of monitoring will cover questionnaire data, monitoring results, and records of deposits and refunds. The primary responsibilities of the DMC are to ensure data integrity, evaluate participant safety, and protect participant rights. All monitoring activities will be conducted in a blinded manner to ensure data objectivity and the reliability of trial results. The DMC has the authority to immediately suspend or terminate the study if any non-compliance with the approved protocol or unauthorized changes in study procedures are detected. The Principal Investigator, Co-Investigators, and designated personnel from the Sponsor’s organization will have access to the final trial dataset. Additionally, external auditors, in addition to the Data Monitoring Committee, may also be granted access.

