## Discussion

8

HPV-based self-sampling has emerged as a promising approach to increase cervical cancer screening coverage, especially in hard-to-reach populations (1). However, a critical challenge remains: the low feedback rate of self-sampling results, which undermines the effectiveness of screening programs (2). Enhancing the feedback rate of HPV self-sampling results is crucial for ensuring that women receive timely diagnosis and treatment, thus improving the overall efficacy of cervical cancer screening (3, 45). Pay-It-Forward interventions have shown potential in improving screening effectiveness by leveraging the psychological effect of commitment (4, 45). This study will explore the application of a Pay-It-Forward approach to increase the feedback rate of HPV self-sampling results, aiming to fill the gap in current screening strategies (1).

This study pioneers the application of the Pay-It-Forward method, a novel economic incentive approach, to improve the feedback rate of HPV self-sampling results. By requiring participants to pre-pay a certain fee, which is refunded upon completion of self-sampling and feedback of results, this model is expected to enhance participants’ motivation and sense of responsibility (46). This psychological commitment effect may lead to a higher feedback rate compared to traditional screening interventions (10, 47). Another innovation of this study lies in its extensive geographical representation and in-depth urban-rural disparity analysis. By covering all urban districts and surrounding counties of the city and equally recruiting participants from each region, we ensure the generalizability and fairness of the study results (15, 48). This design not only reduces selection bias but also promotes health equity by providing equal health intervention opportunities for women in different areas (16).

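### Sections 7.6 and 7.16 claim blinding that a one-arm deposit rules out after assignment; the randomisation as described also does not guarantee the stated 54:54 split or balance by area

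*Protocol article*

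**What the plan says.** On masking, section 7.6 (Randomization) states that "Both the participants and the interveners are unaware of" the group to which each woman is assigned. The sentence stands in the step on sealed envelopes and gives no end point. In the next steps "the researcher sequentially opened the envelopes in accordance with a predefined procedure", and the same researcher records the resulting group.

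On the difference between arms, section 7.7 (Interventions) states that "the intervention group needs to prepay to obtain the kit, while the control group can receive the HPV self-sampling kit without payment". Section 7.8 sets the deposit at 20 RMB, payable before the kit is handed over. Trained staff take the payment and log it with the participant's details. Section 7.9 has the project team verify feedback and the financial officer return the money.

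On the committee, section 7.16 (Data monitoring) states: "The scope of monitoring will cover questionnaire data, monitoring results, and records of deposits and refunds". It also states: "All monitoring activities will be conducted in a blinded manner".

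On the sequence, section 7.6 describes a basic technique at a 1:1 ratio: "The study designer created a sequence of random numbers using the RANDBETWEEN function in Excel". No block, stratum or rule for turning a number into a group is given. Section 7.2 fixes the arms at 54 and 54. Section 7.3 recruits from four urban districts and five counties, and the Discussion speaks of "equally recruiting participants from each region".

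**The concern.** Paying a deposit is the intervention, so women cannot be kept from knowing their arm. That is not a flaw in itself. The flaw is that the article attributes to the trial a protection it does not have. A reader who takes section 7.6 at its word would discount bias from knowledge of the arm in the outcomes most open to it. These are the satisfaction and acceptance questionnaires at T1, which are answered by women who know whether they paid. The same reader would credit the committee with a blinding that its own source records undo.

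The secondary concern is chance imbalance. The article gives reasons to expect return to differ by area: section 4 describes a dispersed population, and section 5 describes poorer access to screening in rural areas. Nothing in the described sequence holds the arms balanced overall or by area. An uneven urban/rural mix between arms would then be mixed into the comparison of return rates unless the analysis allows for it.

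**Working it through.** **Masking, by stage**

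- Before the envelope is opened (7.6): the group is unknown to the woman and to staff. The sentence can be true here.
- Envelope opened and group recorded (7.6): the researcher knows the group.
- Kit handed over (7.7, 7.8): a woman asked for 20 RMB knows her arm, and so do the staff who take and log the payment. The control woman gets her kit without paying.
- Refund (7.9): the project team and the financial officer act on intervention women only.
- Monitoring (7.16): the committee reviews deposit and refund records. By 7.8 these carry participant details, and only intervention women have them. A woman's presence in the log identifies her arm.

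The statement in 7.6 therefore holds at the first stage only. The statement in 7.16 fails wherever the committee can link the deposit log to other data.

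**Split between arms**

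Inputs: N = 108, 1:1 (7.2, 7.6). The planned split is 108/2 = 54 per arm. Assumption: simple randomisation, with each woman assigned independently with probability 0.5.

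- P(54:54) = C(108, 54)/2^108 = 0.077.
- SD of an arm's size = √108/2 = 5.2.
- P(48:60 or worse) = 2 × P(X ≥ 60) = 0.290.
- P(44:64 or worse) = 2 × P(X ≥ 64) = 0.067.

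**Split within areas**

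Assumption: equal recruitment means 108/9 = 12 women in each of the nine areas, so 48 urban and 60 county women.

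- P(9:3 or worse in one area) = 2 × (220 + 66 + 12 + 1)/4096 = 0.146.
- P(at least one of nine areas at 9:3 or worse) = 1 − (1 − 0.146)^9 = 0.758.

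**Cost in power**

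Inputs from 7.5: p1 = 0.617, p2 = 0.90, two-sided α = 0.05. Pooled formula: power = Φ{[|p2 − p1| − 1.96 √(p̄(1 − p̄)(1/n1 + 1/n2))] / √(p1(1 − p1)/n1 + p2(1 − p2)/n2)}, where p̄ is the rate pooled over both arms.

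- 54:54: [0.283 − 1.96 × 0.0824]/0.0777 = 1.56, power 94.1%.
- 48:60: 93.8% to 94.0%, depending on which arm is larger.
- 44:64: 93.2% to 93.6%.

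The loss at 44:64 is 0.5 to 0.9 points.

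**The case against.** The best defence of section 7.6 is its position. The sentence comes directly after the description of the envelopes and before the enrolment step, which is where a protocol describes concealment. Nowhere does the article call the trial single- or double-blind. That reading is probably what was meant, and it stands. It does not rescue the wording, which carries no time limit and names the interveners, who go on to handle the deposit.

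For the committee, it can be said that deposit records could be reviewed apart from outcome data. That is feasible, but the article calls all monitoring blinded and describes no such separation.

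The primary outcome is also fairly well protected. It is kit return within one month taken from laboratory records, and no section describes reminders through which staff could favour an arm.

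A reader might go further and infer any of four things that the article does not support:

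- **That the sequence cannot yield 54:54.** The rule linking numbers to groups is not given. Ranking the numbers and halving the list would give 54:54 every time, and simple randomisation gives it 7.7% of the time.
- **That one envelope series is opened at nine sites at once.** Section 7.3 names nine areas for recruitment. Section 7.6 mentions only a researcher and a predefined procedure, and does not say where the envelopes are held.
- **That the primary analysis is unadjusted.** Section 7.13 names GEE without listing covariates, and Table 1 has a covariate block. The choice may lie in an analysis plan that is not shown.
- **That arm balance by centre is promised.** The Discussion promises equal recruitment by region, which is a different thing. Simple randomisation remains valid.

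**Conclusion.** The masking point holds. Sections 7.6 and 7.16 each state a blinding that other parts of the article contradict. After assignment neither the women nor the staff who run the deposit can be masked, and the committee's listed records identify the arm. What can be claimed is concealment until the envelope is opened. The consequence is greatest for the self-reported T1 outcomes and smaller for the laboratory-recorded primary outcome.

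The randomisation point holds only as a design weakness. As described, the procedure does not guarantee 54:54 or balance by area. The figures of 7.7% and 29% assume simple randomisation, which is inferred from the description. The figures by area further assume 12 women in each of nine areas. The cost in power is small, about one point even at 44:64. What remains is chance imbalance by area, which adjustment can address.

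**What to change.** 1. In section 7.6, replace the masking sentence. State that allocation is concealed from participants and staff until the envelope is opened and that the trial is open-label thereafter. Interpret the T1 satisfaction and acceptance outcomes as reports from women who know their arm. Cost: a few sentences.
2. In section 7.16, either drop the claim of blinding or separate the committee's review of deposit and refund records from its review of outcome data, and say how. Cost: wording, or a modest change in how reports are prepared.
3. Do not substitute a claim that laboratory staff are masked unless this is arranged. Sections 7.7 and 7.10 describe different return routes for the two arms, and the route itself might reveal the group.
4. State the rule that turns a random number into a group, so that a reader can tell whether 54:54 is fixed or only expected.
5. If enrolment has begun (section 7.3 gives a start of January 20, 2025), keep the existing list and adjust the primary comparison for urban/rural area. Two strata are safer than nine small centres, and the data are already at hand. Cost: slightly more analysis work.
6. Only if enrolment has not started, centre-stratified permuted blocks of varying size are an option. They need a new list and an envelope set per centre, and make allocation slightly more predictable at block ends.
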